## Abstract

**Background:**

Despite optimal medical therapy, patients with stable coronary artery disease (SCAD) still have a high risk of recurrent cardiovascular events. Exercise capacity measured by cardiopulmonary exercise testing (CPET) is a good surrogate marker for the long-term prognosis of SCAD. Qixue Tongzhi Granule (QTG) is created by academician [name] and has the function of tonifying qi, promoting blood circulation, and regulating qi-flowing. This trial aims to investigate the efficacy and safety of QTG in improving exercise tolerance, alleviating angina pectoris and anxiety/depression symptoms, promoting health-related quality of life, and reducing the risk of adverse cardiovascular events in subjects with SCAD.

**Methods:**

This is a randomized, double-blind, placebo-controlled trial. 150 SCAD patients with qi deficiency, blood stasis, and liver qi stagnation syndrome are enrolled. Patients will be randomly allocated to the QTG or placebo groups at a 1:1 ratio. QTG and placebo will be added to the modern guideline-directed medical therapy for 12 weeks and patients will be followed up for another 24 weeks. The primary outcome is the improvement of metabolic equivalents measured by CPET. The secondary outcomes are cumulative incidence of composite endpoint events, other indicators in CPET, changes in the Seattle Angina Questionnaire, traditional Chinese medicine syndrome scale, 12 items of Short Form Health Survey Questionnaire, Patient Health Questionnaire-9, and Generalized Anxiety Disorder-7, changes of ST-T segment in the electrocardiogram, improvement of left ventricular ejection fraction and left ventricular end-diastolic diameter in echocardiography. In addition, metabolomics analysis will be performed based on blood samples. Adverse events and safety evaluations will also be documented. A full analysis set, per protocol set, and safety analysis set will be conducted.

**Discussion:**

This clinical trial can enrich treatment options for CHD patients with low cardiorespiratory fitness and psychological imbalance, and it may also create a new situation for promoting the application of traditional Chinese medicine in cardiac rehabilitation.

**Clinical Trial Registration:** [http://www.chictr.org.cn], identifier: [ChiCTR2200058988].

## Introduction

Statistics from the American Heart Association revealed that there were approximately 244 million patients with ischemic heart disease (IHD) and 8.95 million deaths of IHD worldwide in 2020, with an age-standardized IHD mortality rate of 112/100,000 (1). Despite modern guideline-adjusted therapy, patients with stable coronary artery disease (SCAD) still have a high risk of recurrent cardiovascular events (2, 3). Ischemic heart disease remains the leading cause of death worldwide (4, 5). Urgent percutaneous coronary intervention (PCI) is crucial to save the life of patients with acute myocardial infarction. However, compared with conservative medication, the additional increase in life expectancy provided by coronary artery revascularization for SCAD patients is controversial (6, 7). Patients who receive optimal medical treatment still have high residual cardiovascular risk (8); meanwhile, they often complained of recurrent angina pectoris, anxiety, and depressive symptoms, declined exercise tolerance and quality of life, and impaired social function (9–11). The multiple benefits of exercise-based cardiac rehabilitation (CR) on cardiovascular outcomes have been well testified (12). Exercise tolerance refers to the maximum exercise capacity the body can achieve, and it is a strong and independent predictor for all-cause and cardiovascular-specific mortality (13). Cardiopulmonary exercise testing (CPET) can precisely evaluate exercise capacity and functional status (14). At present, drugs that can significantly enhance the exercise tolerance of cardiovascular patients are rare.

In traditional Chinese medicine (TCM), the core pathogenesis of SCAD is “deficiency in origin and excess in superficiality”, while anxiety and depression are associated with liver-qi stagnation. Qi deficiency can lead to blood stasis, and it can also result in qi stagnation. In other words, this is “excess resulting from deficiency”. Based on this theory, Qixue Tongzhi Granule (QTG) is transformed from Xuefu Zhuyu decoration by academician [name]. QTG consists of *Astragali radix*, *Chuanxiong rhizoma*, *Paeoniae radix rubra*, *Corydalis rhizoma*, and *Aurantii fructus*, having the function of tonifying qi, promoting blood circulation, and regulating qi-flowing. During the 8th, 9th, and 10th Five-year National Science and Technology Attack Plan, academician [name]'s team conducted a series of clinical trials to evaluate the effect of optimized formulas of Xuefu Zhuyu decoration, such as Xuefu Zhuyu condensed pills, refined Xuefu capsule, Xiongshao capsule, on preventing restenosis after coronary intervention (15, 16). Declined exercise capacity and fatigue are common clinical manifestations in CHD patients. Evidence from the basic research shows that *Astragali radix* can increase exercise capacity and resist fatigue in mice (17, 18). Moreover, *Astragali radix* can lower cholesterol levels and improve self-reported vigor in older adults (19). Active ingredients extracted from *Paeoniae radix alba*, *Corydalis rhizoma*, *Aurantii fructus*, and *Astragali radix* have antidepressant effects in animal models (20–23).

Under the direction of disease integration with the syndrome theory, we aim to investigate the efficacy and safety of QTG in improving exercise capacity, alleviating angina pectoris, anxiety/depression symptoms, promoting the health-related quality of life, and reducing the risk of composite endpoints in subjects with SCAD. Until now, Chinese and Western medicines verified to be effective in improving aerobic capacity and prognosis of CHD are rare. This study may present a novel, promising treatment option for CHD patients with low cardiorespiratory fitness and psychological imbalance.

## Methods and materials

### Design and settings

This is a multicenter, prospective, randomized, double-blind, placebo-controlled, superiority trial. This trial is registered in the Chinese Clinical Trial Registry (No. ChiCTR 2200058988) and fully complies with the Declaration of Helsinki and Good Clinical Practice (GCP) Guidelines 2020. The protocol has been designed according to SPIRIT 2013 statement and SPIRIT 2013 explanation and elaboration (24, 25). The study was approved by the Research Ethics Committee of Xiyuan Hospital, China Academy of Chinese Medical Sciences (ID: 2021XLA090-3).

This multicenter trial will be conducted at four hospitals in mainland China, including Xiyuan Hospital, Guanganmen Hospital, Wangjing Hospital, and The First Affiliated Hospital of Shanxi University of Chinese Medicine. A total of 150 participants will be recruited. After the participants have provided written informed consent, they will be enrolled in the trial, which consists of a 12-week treatment period and a 24-week follow-up period. The schematic diagram of study procedures is illustrated in Figure 1.

**Figure 1 F1:**
[figure not shown]
Flow chart of the study design. SCAD, stable coronary artery disease; ACEI, angiotensin-converting enzyme inhibitor; ARB, angiotensin receptor antagonist; QTG, Qixue Tongzhi Granule; CPET, cardiopulmonary exercise testing; SAQ, Seattle angina questionnaire; SF-12, 12 items of short form health survey questionnaire; PHQ-9, patient health questionnaire-9; GAD-7, generalized anxiety disorder-7; TCMSS, traditional Chinese medicine syndrome scale; ECG, electrocardiogram; LVEF, left ventricular ejection fraction; LVEDD, left ventricular end-diastolic diameter; UCG, echocardiography; AEs, adverse events; SAEs, severe adverse events; FAS, full analysis set; PPS, per protocol set; SAS, safety analysis set.

### Study population

#### Diagnostic criteria

The diagnostic criteria of SCAD refer to the 2023 AHA/ACC/ACCP/ASPC/NLA/PCNA guideline for the management of patients with chronic coronary disease (26); The diagnosis of TCM syndrome elements of qi deficiency, blood stasis, and qi stagnation follows expert consensus on TCM diagnosis and treatment of stable angina pectoris of coronary heart disease (2018 edition) (China Association of Chinese Medicine).

#### Inclusion criteria

Patients eligible for the trial must comply with all of the following at randomization:
1)Coronary angiography or coronary computed tomographic angiography shows at least one major coronary artery luminal diameter stenosis ≥ 50%, a history of myocardial infarction, or being in a stable condition more than one month after PCI or coronary artery bypass grafting.2)Left ventricular ejection fraction ≥ 40%.3)Canadian Cardiovascular Society grading of angina pectoris is I-II.4)TCM syndrome differentiation is in accord with qi deficiency blood stasis and liver qi stagnation. TCM syndrome diagnosis should have the primary symptoms and at least two accompanying symptoms. Primary symptoms: chest tightness and chest pain; Accompanied symptoms: palpitation, shortness of breath, spontaneous perspiration, fatigue, distension in the hypochondrium, abdominal fullness, heaving a deep sigh, impatience, and irritability.5)Aged 18–75 years.6)Meet low to medium risk stratification of CR and could take part in the CPET.7)Provide written informed consent.

#### Exclusion criteria

Patients who meet any of the following criteria couldn't attend the study:
1)Acute myocardial infarction, unstable angina pectoris, underwent PCI or CABG within the past month.2)Meet absolute and relative contraindications of CPET.3)Patients who have taken botanical drugs for tonifying qi, promoting blood circulation, or regulating qi flowing, or have participated in other clinical trials during the past month.4)Abnormal renal function with an estimated or calculated creatinine clearance < 60 ml/min.5)Patients with severe liver disease or alanine aminotransferase, aspartate transaminase > 3 times the upper limit of normal.6)New York Heart Association class Ⅳ or recurrent malignant arrhythmia.7)Combining with chronic obstructive pulmonary disease, pulmonary infection, or respiratory failure.8)Diabetic patients with random blood glucose ≥ 13.7 mmol/L or glycosylated hemoglobin ≥ 9.5%.9)Pregnancy, preparing for pregnancy, and breastfeeding.10)Patients have acute cerebrovascular disease, malignant tumor, serious hematopoietic system disease, or life expectancy of less than one year.11)Patients with psychosis, severe anxiety, and depression or those who have taken anti-anxiety and depression drugs within the past month;12)Patients are allergic to known ingredients of the study drug.

#### Criteria for withdrawal, dropout, removal

If the subjects occur severe organ dysfunction, drug allergic reaction, disease deterioration, or serious adverse events during the trial, it is necessary to stop participating in the trial according to the judgment of clinicians; participants can also withdraw from the trial voluntarily due to poor efficacy, intolerance of adverse reactions, and desire to try another treatment methods. Of course, participants may withdraw from the study for any reason at any time. Although the subjects do not explicitly propose to withdraw from the study, they no longer receive medications and examinations and are lost to follow-up. Undoubtedly, this is also withdrawn.

Dropout means that randomized patients prematurely discontinue the study and only complete some of the procedures specified in the trial. For patients who were lost to follow-up or withdraw, efforts should be made by telephone or letter to inquire about the reasons for dropping, investigate their medication history and the time of last taking medicine, and record the outcome measurements at the time of discontinuation. Investigators should try their best to keep subjects enrolled in the study and have the following clinical and laboratory evaluations performed.

Participants may be removed if he/she (1) violates inclusion criteria or meets the exclusion criteria, or receive the wrong treatment assignment; (2) has poor treatment compliance or the number of drugs used does not meet the requirements (<80% or >120%); (3) has incomplete data and no evaluable records after randomization; (4) has used drugs that may influence the efficacy and safety evaluation of the study drug. Removal cases should not be included in the efficacy analysis. However, the safety analysis should incorporate those who receive at least one treatment and have at least one safety record.

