#### Data analysis

The statistical analysis will be conducted using SAS software (version 9.4). According to the “intention to treat” principle, the full analysis set (FAS) is defined as all participants randomized in the trial, with at least one experimental drug treatment history and at least one therapeutic session visit. Per protocol set (PPS), exclude participants found to be ineligible after randomization or deviate from the intervention or follow-up protocols. The safety analysis set will include all randomized patients who have completed at least one study visit. Finally, we will draw conclusions according to the analysis results of FAS. PPS will be used for sensitivity analysis.

For quantitative data meeting normal distribution, means with standard deviations will be calculated, otherwise, medians with quartile ranges will be shown. While for qualitative data, frequencies and percentages will be described. Comparison between groups will be performed by independent t-tests, or Wilcoxon rank-sum test for quantitative data, and the chi-square test or Fisher's exact test for qualitative data. Subgroup analyses will be conducted on those with PHQ-9 or GAD-7 scores ≥ 5 or < 5. Confounding factors that are difficult to control and unbalanced between groups will be used as covariates to analyze covariance to eliminate their influence on efficacy evaluation. *P* < 0.05 will be considered statistically significant. The last observation carried forward is supposed to estimate missing outcome data. Regarding safety, the number of AEs and SAEs will be categorized, and the incidence rate will be calculated. The data monitoring committee is not formally established because the trial has a short duration and known minimal risks. However, some form of data monitoring will undoubtedly be conducted by inspectors appointed by PI to ensure the accuracy and integrity of data.

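### The removal rule excludes ineligible, wrongly treated, non-adherent and prohibited-drug participants from the efficacy analysis, whereas the Data analysis section keeps them in the FAS that carries the conclusion

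*Protocol article*

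**What the plan says.** Two sections of the protocol article decide who enters the efficacy analysis.

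**Criteria for withdrawal, dropout, removal.** The list of grounds opens with "Participants may be removed if he/she". There are four:

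- Ground 1, on eligibility and allocation errors: "violates inclusion criteria or meets the exclusion criteria, or receive the wrong treatment assignment".
- Ground 2, on adherence, with limits given as percentages: "has poor treatment compliance or the number of drugs used does not meet the requirements (<80% or >120".
- Ground 3, on absence of anything to analyse: "has incomplete data and no evaluable records after randomization".
- Ground 4, on added medication: "has used drugs that may influence the efficacy and safety evaluation of the study drug".

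The consequence is then stated: "Removal cases should not be included in the efficacy analysis". Only the safety analysis is told to keep these participants.

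**Data analysis.** This section invokes intention to treat. Its main set is introduced as follows: "the full analysis set (FAS) is defined as all participants randomized in the trial, with at least one experimental drug treatment history". Attendance at one or more treatment-period visits is required as well. The PPS leaves out participants found ineligible and those who deviate from the intervention or follow-up, and it serves as a sensitivity analysis. On which set decides, the section says: "Finally, we will draw conclusions according to the analysis results of FAS".

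**The concern.** The first section uses an unqualified term for the efficacy analysis. The second defines an efficacy set without exclusions for eligibility, treatment received, adherence or added drugs, and makes that set decisive. No sentence ranks one section above the other.

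Wrong treatment, adherence and added drugs arise after randomization and may depend on how a patient responds to or tolerates treatment. The same section names poor efficacy, intolerance and the wish to try another treatment as reasons for voluntary withdrawal, so the protocol itself expects behaviour to follow response. If participants are dropped on such grounds, the groups being compared are no longer the groups that were randomized.

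Two details add to this. Removal is optional, so two participants with the same intake can be handled differently. And Table 2 schedules the compliance evaluation at Week 12, the visit of the final CPET, so a participant whose primary outcome has been measured can still be discarded.

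**Working it through.** **Step 1. The two rules side by side, for a randomized participant who took study drug and attended a treatment-period visit**

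| Situation | Removal section | FAS (Data analysis) | PPS (Data analysis) |
|---|---|---|---|
| Found ineligible | may be removed, then out of efficacy | in | out |
| Received wrong treatment | may be removed, then out of efficacy | in | out, as a deviation |
| Intake below 80% or above 120% | may be removed, then out of efficacy | in | out, as a deviation |
| Used drugs that may affect evaluation | may be removed, then out of efficacy | in | out, as a deviation |
| Incomplete data and no evaluable record | may be removed, then out of efficacy | mostly out already, for want of a visit | out |

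The first four rows (grounds 1, 2 and 4) conflict with the FAS. The last row (ground 3) requires both conditions together and largely coincides with the visit requirement of the FAS. The removal column also matches the PPS column, so applying it to the FAS brings the two sets close together.

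**Step 2. The plan's own sample size**

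Inputs from Sample size calculation: difference 1.38 METs, SD 1.56, superiority margin 0.42, one-sided 2.5%, 90% power, 20% dropout, 1:1 allocation.

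- Distance to be detected: 1.38 − 0.42 = 0.96.
- Noncentral t: 57 per arm gives 90.3% power and 56 per arm falls just short (89.8%).
- Dropout: 57 / 0.8 = 71.25, so 72 per arm, or 144 in total.

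The stated 144 is reproduced exactly. No stated figure is wrong; the fault lies in the analysis sets.

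**Step 3. How far removal could move the estimate**

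Let r be the share of an arm removed and g the amount by which the mean MET gain of those removed lies below that of the rest of the arm. Removal raises that arm's mean by r × g, so the estimated difference changes by

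shift = r(QTG) × g(QTG) − r(placebo) × g(placebo).

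The document gives none of these four quantities. Assume removal from the QTG arm only, with g equal to the whole planned effect (the removed participants have no treatment effect) and r = 15%:

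- Kept: 0.85 × 1.38 = 1.173 METs.
- Removed: 1.38 METs.
- Shift: 0.207 METs, and 0.207 / 0.42 = 49% of the margin.

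Over a range of assumptions, still for the QTG arm only:

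| r | g = 0.5 | g = 1.0 | g = 1.38 |
|---|---|---|---|
| 10% | 0.05 | 0.10 | 0.14 |
| 20% | 0.10 | 0.20 | 0.28 |

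The same losses in the placebo arm alone give the same sizes with the opposite sign. Equal losses in both arms cancel.

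**The case against.** The best defence is that the two sections can be harmonised. The removal grounds are almost the PPS exclusions, the Data analysis section governs the analysis, and removal is permitted rather than required, so the efficacy analysis in the removal section may simply mean the PPS. That is a plausible account of what the sponsor intended. But the text does not say it, and an analyst who follows the removal section literally breaks no other instruction on removed cases. The optional wording does not help: it leaves the choice to judgement after randomization. The blind review meeting before database lock (Data collection and management) is a suitable place to settle membership, but the protocol does not assign it that task. Blinding would limit selective choice; it would not undo selection on post-randomization behaviour.

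Several stronger readings are tempting and are not supported:

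- **That participants with incomplete data are dropped.** Ground 3 also requires that no evaluable record exists. Partial data are covered by last observation carried forward.
- **That the bias favours QTG.** The grounds apply to both blinded arms and include excess intake. Removing placebo participants who did poorly and took added drugs would act the other way.
- **That removal costs power.** In the illustration the opposite holds. With 60 per arm and these patients kept, the distance to the margin is 1.173 − 0.42 = 0.753 and power is 74.6%. With 15% removed from both arms (51 per arm) and a difference of 1.38, nominal power is 86.8%. The gain comes from estimating a different, selected effect.
- **That the FAS must become all randomized participants.** Requiring one dose and one visit is a common modified intention-to-treat definition and contradicts nothing else in the document.

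**Conclusion.** The point holds for grounds 1, 2 and 4: as written, the removal section and the Data analysis section give different answers on who is in the analysis that carries the conclusion. If the removal rule is followed, that analysis is close to per-protocol, the randomized comparison can be biased, and agreement between FAS and PPS loses most of its value as a check.

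Neither direction nor size can be derived from the document. The figure of about 0.21 METs against a margin of 0.42 rests on three assumptions: 15% removed, all from the QTG arm, with no treatment effect. Ground 1 is somewhat milder where it concerns eligibility facts fixed before randomization, but it conflicts with the FAS text all the same. The contradiction itself rests on no assumption and is wrong as written.

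**What to change.** In Criteria for withdrawal, dropout, removal, replace the sentence on removal cases with a statement that:

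- the removal grounds define exclusion from the PPS only;
- PPS membership is settled for every participant at the blind review meeting before database lock, with the ground recorded;
- all participants who meet the FAS definition in Data analysis stay in the primary efficacy analysis, in the group to which they were randomized.

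The FAS definition and the sample size of 144, rounded to 150, need not change. The change is a text correction with no new visits or data.

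The cost is statistical: the FAS estimate and its power may be less favourable than in a selected set. If a share of the QTG arm is kept and has no treatment effect, the expected difference is 0.90 × 1.38 = 1.24 METs at 10% and 0.80 × 1.38 = 1.10 METs at 20%. Power with all 75 per arm analysed is then about 89% and 76%, against 96% with no such participants.

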### Randomization, allocation concealment, and blinding

#### Random allocation

All patients who consent to participate and fulfill the inclusion criteria will be randomly assigned to the control or QTG group with a 1:1 allocation ratio. An independent statistician will generate the randomization sequence using center-stratified block randomization via SAS software (version 9.4). Treatment allocations will be put into opaque sealed envelopes sequentially numbered 1 to 150. A statistician will send the blind codes directly to the drug manufacturing room to label investigational products. Treatment allocation will not be disclosed until the primary endpoint is analyzed to ensure concealment. According to the clinical study program, the randomized code of drugs is the unique identification code of participants.

